## Abstract

**Background:**

Mood disorders (anxiety, depression), sleep disorders, and catastrophizing lead to increased post-operative pain perception, increase in postoperative opioid consumption, decreased engagement with physical activity, and increased resource utilization in surgical patients. Psychosocial disorders significantly affect postoperative outcome. Unfortunately, studies focused on perioperative psychological assessment and treatment are scarce. We propose to test whether digital cognitive behavioral intervention (dCBI) can help surgical patients. dCBI such as RxWell™ is a proven treatment for mood disorders in medical patients such as reducing depression in patients with inflammatory bowel disease. We hypothesize that RxWell™ will also be effective in surgical patients. This study aims to test whether RxWell™ can improve preoperative mood disorders and subsequently reduce postoperative pain and opioid requirement in patients scheduled for primary total hip and knee arthroplasty (THA, TKA). We named the trial as the SuRxgWell trial.

**Methods:**

This is a randomized, controlled trial that will enroll primary and unilateral THA or TKA patients with anxiety and/or depression symptoms before surgery to receive the SuRxgWell dCBI program and investigate its impact on postoperative outcomes including postoperative pain, anxiety, depression, sleep disorder, and catastrophizing. After signing an informed consent, subjects will be screened using the PROMIS questionnaires, and subjects with a T-score of ≥ 60 on the short Patient-Reported Outcomes Measurement Information System (PROMIS) 4a Anxiety and/or short PROMIS 4a Depression questionnaires will be randomized to either usual care (control group) or the cognitive behavioral intervention, *RxWell*™, plus usual care (intervention group). The control group will receive information on how to locate tools to address anxiety and depression, whereas the intervention group will have access to SuRxgWell 1 month prior to surgery and up to 3 months after surgery. The allocation will be 3:1 (intervention to control). Investigators will be blinded, but research coordinators approaching patients and research subjects will not.

The primary outcome will be day of surgery anxiety or depression symptoms measured with the PROMIS Short Form v1.0 -Anxiety 4a/Depression and Generalized Anxiety Disorder Measure (GAD-7) and Patient Health Questionnaire (PHQ-8). Secondary end points include measuring other health-related quality of life outcomes including sleep disturbance, fatigue, ability to participate in social roles, pain interference, cognitive function, pain catastrophizing, and physical function. Other secondary outcomes include collecting data about preoperative and postoperative pain scores, and pain medication usage, and orthopedic functional recovery at baseline, day of surgery, and 1, 2, and 3 months after the surgery with the Pain Catastrophizing Scale, the Knee injury and Osteoarthritis Outcome Score (KOOS), and Hip injury and Osteoarthritis Outcome Score (HOOS). In addition, subjects will be asked to complete a GAD-7 and PHQ-8 questionnaires bi-weekly (via the *RxWell*™ app for the interventional group or REDCAP for the control group). Data about postsurgical complications, and resource utilization will also be recorded. We will also receive monthly reports measuring the usage and engagement of RxWell use for each participant randomized to that arm. The primary hypotheses will be assessed with intention-to-treat estimates, and differences in primary outcome will be tested using independent two sample *t*-tests. This trial is registered to the ClinicalTrials.gov database (NCT05658796) and supported by the DAPM, UPMC Health Plan, and the NIH.

**Discussion:**

Our trial will evaluate the feasibility of digital cognitive behavioral intervention as a perioperative tool to improve anxiety and depression before and after major orthopedic surgery in comparison to education. If digital cognitive behavioral intervention proves to be effective, this might have important clinical implications, reducing the incidence of chronic postsurgical pain and improving outcomes.

**Supplementary Information:**

The online version contains supplementary material available at 10.1186/s13063-023-07634-0.

## Background

The optimization of perioperative care reduces postoperative complications and undesirable sequelae of surgery such as pain, fatigue, depression, resource utilization, and prolonged convalescence [1]. Patients scheduled for surgery often present with co-occurring mood disorders, such as generalized anxiety, major depression, and/or high levels of pain catastrophizing [2]. These are particularly salient among patients scheduled for primary total hip and knee arthroplasty (THA, TKA), procedures that are expected to increase by 71%, to 635,000 procedures, by 2030 (THA) and by 85%, to 1.26 million procedures, by 2030 (TKA) [3].

Almost 30% of patients undergoing a TKA surgery experience psychological distresses preoperatively [4]. These emotional conditions negatively impact postoperative pain and opioid consumption, post-surgical complications rate, recovery time, and re-hospitalization rate [5–14]. Although preliminary data demonstrate that advances in perioperative medicine such as the use of multimodal and multidisciplinary interventions appear to control perioperative surgical stress response and improve postoperative outcomes, this is insufficient. Optimization of physiology, such glycemic control in diabetic patients or blood pressure management in patients with hypertension, is systematically performed, and yet surgical outcomes can be improved. An often-overlooked opportunity for improving surgical care is optimizing a patient’s preoperative emotional condition. The pathophysiological link between psychological factors and surgical outcomes has been widely described [15]. Unfortunately, studies focusing on perioperative psychological assessment and treatment are lacking. Non-physical preoperative patient factors may directly influence the neuroendocrine and inflammatory response to surgical stress, impacting on immune function and healing, the development of cardiovascular diseases, and neurological events [16–19].

Surgical patients with mood disorders result in longer in-hospital length of stays, higher incidence and odds of readmission, higher rate of medical and implant-related complications, and higher day of surgery and 90-day peri-surgical costs [20, 21]. Mood disorders also increase peri-operative pain, opioid requirement, and delay recovery. The high prevalence of anxiety and depression in patients undergoing total hip and knee makes mood disorders meaningful potential targets for preoperative patient optimization [22]. However, studies analyzing the impact of a preoperative psychological assessment and intervention in orthopedic surgery are missing. Mood disorders can be efficiently assessed using brief screening methods such as the Hospital Anxiety and Depression Scoring (HADS) or PROMIS (Patient-Reported Outcomes Measurement Information System). The PROMIS library has short forms for depression and anxiety and has the added advantage of being validated across different patient populations. Interventions focusing on managing mood disorders could be implemented to improve perioperative outcomes. The FDA recommends cognitive-behavioral intervention (CBI) as a first-line treatment for the non-pharmacologic treatment of depression and anxiety, and this could be a potential intervention for reducing mood disorders and pain levels in surgical patients [23–25]. In-person CBI has been described as an effective tool for reducing the Pain Catastrophizing Scale score and Postoperative General Anxiety Disorder-7 scores; decreasing postoperative pain, opioid use, and length-of-stay at the hospital; and increasing functionality based on Knee Outcome Survey – Activities of Daily Living scale (KOS-ADL) in patients undergoing TKA [26–28]. However, multiple barriers exist preventing surgical patients from accessing CBI, such as high costs and lack of accessibility in remote areas [29].

Telemedicine represents increasingly common strategies for patient care. Similarly, digital Cognitive Behavioral Intervention (dCBI) could be an effective strategy for overcoming some of these barriers. There is preliminary data suggesting that dCBI could be an effective treatment for depression and anxiety in primary care [30]. However, the implementation of dCBI for reducing perioperative psychological and psychosomatic conditions is limited. RxWell™ is an app that includes evidence-based cognitive behavioral techniques and can be used remotely to teach coping strategies based on CBI. It has proven to successfully help patients with inflammatory bowel disease [31].

We are using the RxWell™ dCBI in this clinical trial among orthopedic patients and named the trial as SuRxgWell. In this SuRxgWell trial, we hypothesize that the use of RxWell™ will reduce the deleterious impact of established mood disorders on recovery following primary total hip and total knee replacements by improving the following postoperative outcomes:Pain and opioid requirement,Improved functional recovery,Decrease complications, andReduce resource utilization such as hospital length of stay, postoperative need for visits, and the use of rehabilitation.

## Materials and methods

### Study design

This is a prospective, randomized, controlled clinical trial in a multi-hospital health care system among patients with high levels of anxiety with an indication for primary total hip or knee arthroplasty. We will be comparing two groups: one that receives access to RxWell™ and usual care and one that only receives the usual care. Figure 1 and Table 1 show the study design, timing of pre- and postoperative use of RxWell™, and follow-up evaluations. CONSORT 2010 items and CONSORT-SPI 2018 checklist are presented for the abstract (Table 2) and main text (Table 3). The SPIRIT Checklist is presented as an additional file (Additional file 1). We will recruit patients from 4 hospitals within the *UPMC system* (*UPMC Shadyside*, *Magee*, *East*, and *Passavant hospitals*). In this pilot, randomized feasibility trial, we will prospectively allocate 34 subjects in the control group, and using a 1:3 allocation, we will have 102 in the intervention group (two-sided *t*-test with alpha of .05, power of .8, with a 3:1 ratio and a 50% drop out rate for a Cohen’s *d* of .8). A block randomization schedule generated using the R software (version 4.2.1, R Core Team, 2022) will be used to allocate the participants to either dCBI plus usual care (*intervention*) or usual care (*control*) with a 3:1 allocation (Table 2). Investigators will be blinded for group assignment in REDCap, and they will also be blinded for the monthly reports. Research coordinators, the statistical data analysts, and subjects will not be blinded. To make sure investigators are blinded to the intervention, investigators will not have access to the randomization table and surveys in REDCap. Investigators will only be able to access the eligibility checklist and informed consent surveys in REDCap. Patients will be randomized immediately after the PROMIS Anxiety 4a and the PROMIS Depression 4a patient assessment by a research coordinator using REDCap. We do not anticipate any requirement for unblinding, but if required, the director of clinical research operations, regulatory specialist, study coordinators, or the principal investigator will have access to group allocations and any unblinding will be reported.

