### Outcome measures

We will assess the following:RxWell™’s acceptance by practitioners and patients will be measured by qualitative interviews among all practitioners and randomly selected patients.Workflow changes brought on by the implementation of RxWell™, andImpact of RxWell™, on mood disorders (anxiety, depression, pain catastrophizing) in the immediate pre- and post-operative periods.

We will also test the impact of RxWell™, onSleep disordersFatigueAbility to participate in social rolesPain interferenceCognitive functionPerioperative painOpioid requirements and opioid morphine equivalents,Functional recovery, andResource utilization associated with the surgery and recovery (hospital length of stay, duration of physical therapy).

Ultimately, our outcome is to determine if RxWell™ can improve surgical outcomes.

Primary and secondary outcomes will be measured at baseline preoperatively, on the day of the surgery, and 1, 2, and 3 months after surgery (Table 1). Preoperative data will be collected virtually via REDCap surveys by study team members. Postoperative data collection will be performed via email surveys and telephone calls by a member of the study team. Research coordinators collecting outcomes will not be blinded to group assignment. Patients will not be blinded and will be informed that the study aims to assess the effect of dCBI in addition to usual care compared to usual care alone on surgical patients.

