### Data collection procedure (recruitment and data collection procedure)

#### Recruitment and retention

Patients scheduled for their pre-operative evaluation at the Center for Perioperative Care clinics or at the orthopedic clinic will be screened for eligibility, and those deemed eligible will be approached by the study coordinators for recruitment or given a flyer by nurse practitioners or physician assistants. Patients who are interested will be able to consent with an investigator or a research coordinator in person, reach out to the research team, and use the QR code that appears on the flyer to give their contact information, or they will be called by a study team member.

Participants will be able to sign the informed consent via REDCap through a virtual interview with the principal investigator or in person with an investigator or research coordinator. In the case of the e-consent, virtual interviews will be conducted remotely using HIPAA-compliant *Zoom* and following a semi-structured format to ensure a systematic yet flexible approach. On the consent form, participants will be asked if they agree to use of their data should they choose to withdraw from the trial. Participants will also be asked for permission for the research team to share relevant data with people from the university taking part in the research or from regulatory authorities, where relevant. This trial does not involve collecting biological specimens for storage.

Once patients provide consent, we will use the PROMIS questionnaires to assess their mood condition and identify those with high levels of anxiety and depression. They will be eligible if they have a *T*-score ≥ 60 on the PROMIS Anxiety Short Form 4a v1.0 questionnaire and/or PROMIS Depression 4a Short Form v1.0 questionnaire. Participants who meet this criterion will be enrolled and randomized into perioperative treatment with a RxWell™ and usual care or only usual care.

To promote participant retention and compete follow-up, the weekly trial meetings will identify potential data loss and prompt the study coordinators and coaches to reach out to subjects to engage them.

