#### Surveys employed

The full survey, including the four questionnaires, is expected to be completed in no more than 15 min. REDCap will host all surveys.

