#### Data collection

Initially, participants will complete a demographic, lifestyle, and diagnostic survey, consisting of age, gender, ethnicity, race, height, weight, smoking/alcohol use, medical history, ongoing treatments, and comorbidities.

At the baseline, participants from both groups (intervention and education group) will also complete the PROMIS 29+2 v2.0 form, except the Anxiety and Depression subsection since it will have been already completed during the eligibility assessment, the GAD-7 and PHQ-8 scales, the Pain Catastrophizing Scale (PCS), the Knee injury and Osteoarthritis Outcome Score (KOOS), and Hip injury and Osteoarthritis Outcome Score (HOOS) and the Pain Medications Survey and Pain Scores Survey created in REDCap (Table 1).

Participants will be assessed with the same instruments on the day of surgery. In addition, participants allocated in the intervention group will be assessed with the GAD-7 and PHQ-8 bi-weekly through the RxWell™ application during its use.

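### Most baseline questionnaires are completed after randomisation by unblinded patients, which weakens the secondary baseline comparisons but not the primary test

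*Protocol article*

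**What the plan says.** Study design places allocation directly after the two screening forms: "Patients will be randomized immediately after the PROMIS Anxiety 4a and the PROMIS Depression 4a patient assessment by a research coordinator". Recruitment and retention gives the same order. After consent and the PROMIS screen, "Participants who meet this criterion will be enrolled and randomized into perioperative treatment", with no other questionnaire in between.

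Data collection then describes the baseline battery: "At the baseline, participants from both groups (intervention and education group) will also complete the PROMIS 29+2 v2.0 form". The same sentence adds GAD-7, PHQ-8, the Pain Catastrophizing Scale, KOOS/HOOS and the pain and medication surveys. It leaves out only the PROMIS anxiety and depression items, because they were answered at eligibility.

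On blinding, Study design says "Research coordinators, the statistical data analysts, and subjects will not be blinded", and Outcome measures says "Patients will not be blinded and will be informed that the study aims to assess the effect of dCBI".

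**The concern.** A baseline value serves as a reference because allocation cannot have influenced it. Here nearly all of the baseline is self-report, and the plan places it after allocation in an open-label trial. A patient who has just been told they will not receive the app may report more distress. A patient who has the app may already be using it: the abstract gives access from 1 month before surgery, while Table 1 puts baseline at 3–4 weeks before.

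If either happens, the arms can differ at baseline for a reason other than chance, and improvement is measured from a starting point that has already moved. This matters because the Sample size calculation section justifies the unequal allocation partly by more precise estimates of improvement within the treated group. It also describes the trial as a pilot for a later RCT, so the order of procedures could be carried forward.

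**Working it through.** **1. Order of events, place by place**

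- Study design: PROMIS Anxiety 4a and Depression 4a, then randomisation at once.
- Recruitment and retention: consent, PROMIS criterion met, then enrolment and randomisation.
- Table 1: the eligibility column marks only the two PROMIS 4a forms. GAD-7, PHQ-8, the rest of PROMIS 29+2, catastrophizing, pain, medication use and HOOS/KOOS all begin in the enrolment/baseline column.
- Data collection: the battery is completed at baseline by members of both groups.

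The four places agree, and no text shown puts the battery before allocation. The only values certain to precede allocation are the two screening PROMIS scores. Two of the four primary scales, GAD-7 and PHQ-8, therefore have no pre-allocation value.

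**2. A discrepancy on PROMIS 4a**

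Table 1 marks both PROMIS 4a forms at eligibility and again at baseline. Data collection says they are not repeated at baseline. If they were repeated, the second reading would also follow allocation.

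**3. Which analyses use a baseline score (Data analysis section)**

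- Primary: two-sample t-tests of the four scales on the day of surgery. No baseline score enters.
- Covariate rule: standardized mean differences are calculated for patient characteristics, comorbid conditions and details of the operation, and models adjust for demographics above 0.2. Questionnaire scores are not part of this rule.
- Secondary: mixed models over all time points. Exposed.
- Secondary: between-group tests of secondary outcomes, with baseline listed among the time points. Exposed.
- Within-group improvement, as relied on in the Sample size calculation section. Exposed for every scale except the screening PROMIS.

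**4. Direction and size**

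Take a scale on which higher is worse, such as GAD-7 or PHQ-8. Let B be the undisturbed baseline mean in both arms, and F_I and F_C the follow-up means. Early app use lowers the recorded app-arm baseline by d_I. Disappointment raises the recorded control baseline by d_C.

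- App-arm improvement: (B − d_I) − F_I = true improvement − d_I
- Control improvement: (B + d_C) − F_C = true improvement + d_C
- Difference in improvement: true difference − (d_I + d_C)
- Day-of-surgery contrast: F_C − F_I. B does not appear, so the bias by this route is 0.

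Both mechanisms make the app look less effective. The documents give no value for the shift, so the following is an assumption: d_I + d_C between 0.1 and 0.3 SD.

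- A contrast of change from baseline, including a group-by-time contrast in a mixed model with baseline among the outcomes, is biased by the full 0.1 to 0.3 SD.
- A model that conditions on the baseline score is biased by about r times the shift, where r is the baseline-to-follow-up correlation. With r assumed between 0.3 and 0.7, this is 0.3 × 0.1 = 0.03 SD to 0.7 × 0.3 = 0.21 SD.

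The article does not give the form of the mixed model, so both cases are shown. They illustrate the range and do not estimate what will happen.

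**5. Sample size**

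The stated 136 reproduces. For d = 0.8, two-sided alpha 0.05, 80% power and a 3:1 ratio, 17 + 51 = 68 evaluable patients are needed (noncentral-t power 80.4%), and 68 / 0.5 = 136. Nothing in this point changes that figure.

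**The case against.** The strongest reply is that the consequences are small. The primary tests use no baseline. Both plausible mechanisms work against the app, so a positive secondary result would, if anything, be conservative. This stands and limits the weight of the point. It does not remove it: a pilot meant to inform a larger trial also needs its improvement estimates undistorted, and a baseline difference could no longer be read as chance.

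Second, knowledge of the arm at baseline is inferred. No section says when patients are told, the workflow figure is not shown, and the both-groups wording may only mean that the battery is the same in each arm. That is fair. Even so, immediate randomisation, no blinding of patients or coordinators, and agreement across four places make the inference strong. The order itself is stated, so this is not a detail that a condensed article has merely left out.

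Third, the PROMIS discrepancy may be harmless, since Table 1's second mark could be the screening score carried forward. That is possible, and the documents should then say so.

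Fourth, making randomisation conditional on a finished battery selects better responders. This is a real cost, taken up under the fix.

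Two stronger readings are tempting and are not supported. A reader might infer that the primary result is biased because GAD-7 and PHQ-8 are primary scales, and might set a hypothetical baseline shift against the smallest difference the primary t-test could declare significant. That test compares day-of-surgery scores only, so the comparison mixes two different analyses. A reader might also infer that a shift of 0.2 SD would trigger the plan's adjustment rule. That rule covers demographics, which learning one's allocation cannot alter.

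**Conclusion.** The point holds in a limited form. As written, the baseline battery other than the screening PROMIS Anxiety and Depression forms comes after randomisation, in patients who are unblinded and probably aware of their arm. The primary day-of-surgery tests, the demographic adjustment rule and the sample size are unaffected.

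The secondary mixed models over all time points, the secondary-outcome comparisons at baseline, and improvement from baseline on the affected scales are open to a bias of unknown size. Its likely direction is to understate the app's benefit. The 0.1 to 0.3 SD range is an assumption. The conclusion rests on the stated order and on the inference that allocation is disclosed before the battery is completed. The change is worth making because it is standard and cheap and removes the problem entirely.

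**What to change.** In REDCap, keep the randomisation step closed until the whole baseline battery has been submitted, so that the order is consent, PROMIS screen, full battery if eligible, randomisation, disclosure of arm. If this is already the practice, the Study design, Recruitment and retention, and Data collection sections should say so.

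Name the screening PROMIS Anxiety and Depression 4a scores as the baseline for those scales. Reconcile Table 1's second PROMIS 4a mark with the Data collection section, either by removing it or by stating that it is the screening score carried forward.

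The cost is a reordering of forms and a minor amendment. Surveys employed says the full survey "is expected to be completed in no more than 15 min". That sentence refers to four questionnaires while the battery lists more instruments, so the time should be confirmed. Eligible patients who do not finish would not be randomised, which slightly favours better responders. They should be counted and shown when the trial reports against its targets of at least 50% of eligible patients enrolled and at least 60% of enrolled patients completing the questionnaires.
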